#### 4.4 Assessments 2 weeks, 1 month and 2 months after the end of the treatment

**Efficacy variables:** Lesion size / epithelization grade / size of the infiltration in the lesion  
Photograph of each lesion  
Leishmania parasitology  
Response to study treatment

#### 4.5 Assessments 6 months after the end of the treatment

**Efficacy variables:** Lesion size / epithelization grade / size of the infiltration in the lesion  
Photograph of each lesion  
Leishmania parasitology

**Variable security:** Vital parameters  
Laboratory parameters (CBC, clinical biochemistry)

**Overall Assessment** Results of the study and response to therapy

#### 4.6 Flowchart

|                                                          | Visit | 1 a) | 2     | 3     | 4      | 5      | 6 b)         | 7                                | 8                                | 9                                 | 10                                | 11                                |
|----------------------------------------------------------|-------|-----------------|-------|-------|--------|--------|-------------------------|----------------------------------|----------------------------------|-----------------------------------|-----------------------------------|-----------------------------------|
| Evaluation                                               | Day   | Before therapy  | Day 1 | Day 7 | Day 14 | Day 21 | Day 28 or final therapy | 2 weeks after the end of therapy | 1 month after the end of therapy | 2 months after the end of therapy | 4 months after the end of therapy | 6 months after the end of therapy |
| Informed consent                                         |       | x               |       |       |        |        |                         |                                  |                                  |                                   |                                   |                                   |
| Medical history                                          |       | x               |       |       |        |        |                         |                                  |                                  |                                   |                                   |                                   |
| History leishmaniasis                                    |       | x               |       |       |        |        |                         |                                  |                                  |                                   |                                   |                                   |
| Parasitology (fecal / blood)                             |       | x               |       |       |        |        |                         |                                  |                                  |                                   |                                   |                                   |
| Pregnancy test (women of childbearing age)               |       | x c) |       |       | X      |        |                         |                                  |                                  |                                   |                                   |                                   |
| HIV Testing                                              |       | x               |       |       |        |        |                         |                                  |                                  |                                   |                                   |                                   |
| Effectiveness                                            |       |                 |       |       |        |        |                         |                                  |                                  |                                   |                                   |                                   |
| - Parasitology                                           |       | x               |       |       |        |        | x                       | x                                | x                                | x                                 | x                                 | x                                 |
| - Size / degree of epithelization / area of infiltration |       | x               |       | x     | x      | x      | x                       | x                                | x                                | x                                 | x                                 | x                                 |
| - Photo d)                                    |       | x               |       |       | x      |        | x                       | x                                | x                                | x                                 |                                   | x                                 |
| Laboratory:                                              |       |                 |       |       |        |        |                         |                                  |                                  |                                   |                                   |                                   |
| - CBC                                                    |       | x               |       | x     | x      | x      | x                       |                                  | x                                |                                   |                                   |                                   |
| - Biochemistry                                           |       | x               |       | x     | x      | x      | x                       |                                  | x                                |                                   |                                   |                                   |
| - Urine type 1                                           |       | x               |       |       |        |        | x                       |                                  | x                                |                                   |                                   |                                   |
| - ECG (control patients)                                 |       | x               |       |       |        |        | x                       |                                  |                                  |                                   |                                   |                                   |
| Vital signs                                              |       | x               | x     | x     | x      | x      | x                       |                                  | x                                | x                                 | x                                 | x                                 |

a Within the 14 days before the 1st dose (except for parasitological examination of lesions, which will be valid within the last 4 weeks)

b It should be evaluated fully when treatment is discontinued. The reason (s) for discontinuation is (are) documented (s). This applies also to patients who withdrew from the study due to any reason.

c Evaluation of selection performed in the first half of the menstrual cycle (<10 days of the cycle) in the case of a negative pregnancy test before randomization, the treatment can be initiated without waiting period.

Evaluation of selection performed in the second half of the menstrual cycle (> 10 days) pregnancy test followed by a waiting period of two weeks, during which they should be used adequate contraception. After the waiting period should be performed a confirmatory test of pregnancy, before randomization.  
d It should be taken a standard photo (in accordance with the procedure approved by the center) of each lesion.

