|                     |                                                                                                                                                                                                     |                       |                                        |
|---------------------|-----------------------------------------------------------------------------------------------------------------------------------------------------------------------------------------------------|-----------------------|----------------------------------------|
| Study Type   | Interventional                                                                                                                                                                                      | Clinical phase | II                                     |
| Study Design | Allocation: Randomized
Control: Active Control
Endpoint Classification: Safety/Efficacy Study
Intervention Model: Parallel Assignment
Masking: Open Label
Primary Purpose: Treatment | Project        | Miltefosine in Cutaneous Leishmaniasis |

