## 2. OBJECTIVES

The objective of this trial is to assess if therapeutic activity and safety of oral miltefosine patients with CL caused by *L. braziliensis* in an endemic area of Bahia state is similar or superior to the standard treatment (meglumine antimoniate – Glucantime®).

Primary endpoint:

- Rate of final cures (6 month after treatment)

Secondary endpoints:

- Rate of initial cure (2 month after treatment)
- Incidence and severity of adverse events

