### 3.2 Study population

It is planned to include in this study 90 patients, with 30 patients in Group 1 (2 to 12 years old) and 60 patients in Group 2 (13 to 65 years old). Of this total, 60 patients will receive the study drug (Miltefosine), while the remaining 30 will be part of the control group (receive Glucantime®). Ratio miltefosine / standard : 2/1.

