#### 3.2.2 Exclusion criteria

*Safety concerns:*

- Thrombocyte count  $<30 \times 10^9/l$
- Leukocyte count  $<1 \times 10^9/l$
- Hemoglobin  $<5 \text{ g}/100 \text{ ml}$
- ASAT, ALAT, AP  $\geq 3$  times upper limit of normal range
- Bilirubin  $\geq 2$  times upper limit of normal range
- Serum creatinine or BUN  $\geq 1.5$  times upper limit of normal range
- Evidence of serious underlying disease (cardiac, renal, hepatic or pulmonary)
- Immunodeficiency or antibody to HIV
- Severe protein and/or caloric malnutrition (Kwashiorkor, Marasmus).
- Any non-compensated or uncontrolled condition, such as active tuberculosis, malignant disease, severe malaria, HIV, or other major infectious diseases
- Lactation, pregnancy (to be determined by adequate test) or inadequate contraception in females of childbearing potential for treatment period plus 2 months

*Lack of suitability for the trial:*

- Any history of prior anti-leishmania therapy
- Any condition which compromises ability to comply with the study procedures
- Concomitant serious infection other than cutaneous

*Administrative reasons:*

- Lack of ability or willingness to give informed consent (patient and/or parent / legal representative)
- Anticipated non-availability for study visits/procedures

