#### *Documentation of security parameters for routine*

A value outside the normal range or reference in a routine safety assessment, such as laboratory tests, vital signs, ECG, can mean an adverse finding. If the investigator finds that the abnormality has a major relevance, it must also register it in Adverse Event case report form. If the findings contribute to a clinical diagnosis (eg., Hepatitis, in the case of elevated liver enzymes), then this diagnosis should be recorded as an adverse event.

An abnormality should be considered an important clinical relevance if:

represent a serious adverse event, or led to premature discontinuation of the study, or required a therapeutic measure.

With respect to laboratory safety parameters, the investigator must classify each value outside the normal range at:

1. Abnormal but of secondary importance.
2. Abnormal and important relevance (seriously, leading to discontinuation, required a therapeutic measure) should be made to their record in the clinical record.
3. Invalid value, must be specified the reason for this trial.

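### ECGs are scheduled for control patients only, so silent ECG findings can surface by schedule in one arm only, and the baseline ECG presupposes that allocation is known

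*Protocol*

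**What the plan says.** The ECG row of the flowchart (section 4.6) reads "ECG (control patients" and is marked at Visit 1 and Visit 6. Section 3.2 identifies the two groups: "60 patients will receive the study drug (Miltefosine", "while the remaining 30 will be part of the control group (receive Glucantime". No ECG is scheduled for the miltefosine patients, and sections 4.1 to 4.5 do not mention ECG.

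Section 3.4 includes abnormal ECG findings in its definition of an adverse event. Under the documentation of routine safety parameters it adds: "A value outside the normal range or reference in a routine safety assessment, such as laboratory tests, vital signs, ECG, can mean an adverse finding". The abnormality goes on the adverse-event form if the investigator judges it of major relevance, meaning that it was serious, led to premature discontinuation or required a therapeutic measure.

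Section 2 lists "Incidence and severity of adverse events" as a secondary endpoint and aims to show that activity and safety are similar or superior to standard treatment. The design table states "Masking: Open Label".

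On timing, flowchart footnote a places Visit 1 within 14 days before the first dose, and footnote c places pregnancy testing before randomisation. Section 3.2.3 treats withdrawals before first exposure as failures of selection.

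**The concern.** An adverse-event comparison is fair only if both arms have the same chance of showing an event. Here one class of event, the ECG abnormality without symptoms, is looked for on a schedule in the antimony arm and not in the miltefosine arm. Any such event that is recorded adds to the control arm's incidence alone, so the bias favours miltefosine. No later analysis can recover ECGs that were never taken.

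The second issue is timing. Nobody is a control patient until randomised, yet the row is marked at the pre-therapy visit. It can be carried out as written only once allocation is known, in an open-label trial. Section 3.2.2 excludes any patient with "Evidence of serious underlying disease (cardiac, renal, hepatic or pulmonary", a criterion for both arms. If a control patient were removed on that ECG before dosing, section 3.2.3 could class a randomised patient as a failure of selection. No miltefosine patient could be lost in that way.

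**Working it through.** The plan states no figure for ECG findings, so there is none to reproduce. The arm sizes agree with the stated ratio, "Ratio miltefosine / standard : 2/1": 60 + 30 = 90 and 60/30 = 2.

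**Scheduled ECGs.** Antimony: 2 visits × 30 patients = 60. Miltefosine: 0 × 60 = 0.

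**How few findings would look like a difference.** Take x control patients with an event found only by scheduled ECG, and none under miltefosine.

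- x = 2: Fisher p = C(30,2)/C(90,2) = 435/4,005 = 0.109.
- x = 3: Fisher p = C(30,3)/C(90,3) = 4,060/117,480 = 0.035. The other possible splits of three events are all more probable, so this is also the two-sided value.

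Three events are therefore enough at the two-sided 0.05 level.

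**How often that could happen with no true difference.** Assumptions: the true rate p of recordable silent abnormalities is the same in both arms, every one found is counted, and none is found without a scheduled ECG. The chance of a spurious difference is then P(X ≥ 3) with X ~ Binomial(30, p). The protocol gives no value for p, so a range is shown.

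| Assumed p | Expected found, antimony (30p) | Expected unseen, miltefosine (60p) | P(X ≥ 3) | Chance of Fisher p ≤ 0.05 if both arms had the same ECGs |
|---|---|---|---|---|
| 5% | 1.5 | 3 | 18.8% | 2.3% |
| 10% | 3 | 6 | 58.9% | 3.1% |
| 20% | 6 | 12 | 95.6% | 3.7% |
| 30% | 9 | 18 | 99.8% | 3.7% |

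The result falls quickly at lower rates. At p = 2%, P(X ≥ 3) = 1 − 0.98³⁰ − 30(0.02)(0.98²⁹) − 435(0.02²)(0.98²⁸) = 1 − 0.545 − 0.334 − 0.099 ≈ 2%. The major-relevance rule pushes the recordable rate down, so the table shows a mechanism and does not estimate the bias.

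**Timing, passages side by side.**

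1. Section 3.3.2 numbers eligible patients and allocates treatment from a randomisation list, so selection precedes allocation. Footnote c agrees.
2. The flowchart marks the ECG at Visit 1 for control patients, a status that exists only after step 1.
3. Footnote a counts its 14 days back from the first dose, not from randomisation. A post-allocation, pre-dose ECG fits that window, so the row is workable but only after allocation.
4. Section 3.2.3 draws the line between withdrawal and failure of selection at first exposure, not at randomisation. A patient removed between the two falls on the failure-of-selection side.

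**The case against.** There is a fair case on the other side.

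- **Targeted monitoring has a stated reason.** Section 5.2 names cardiac arrhythmias among antimonial toxicities and gives miltefosine's main effects as gastrointestinal, hepatic and renal. This explains the schedule, and part of any ECG difference could be real. It does not make a monitored arm comparable with an unmonitored one.
- **The miltefosine arm is not unobserved.** A reader might infer that cardiac events cannot be recorded there at all. The protocol does not support that. Patients are asked about problems at each visit, pulse and blood pressure are recorded in both arms, and additional tests are allowed when clinically indicated (stated under laboratory tests). Only silent findings on scheduled ECGs are unequally detected.
- **Few silent changes may qualify as adverse events.** The major-relevance rule is strict, and the only on-study ECG comes at the end of therapy, when it can seldom cause discontinuation. This stands, and it is why no size can be given.
- **No passage makes the ECG an eligibility test.** Section 4.1 lists the assessments that verify the criteria and omits ECG. The baseline tracing may simply be a reference for Visit 6. The differential-removal route is open but not stated.
- **Tabulation rules can sit in a SAP.** That is true, and their absence is not the point. The arm-specific schedule is fixed in the protocol, and the source of each event must be captured when it is recorded.

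**Conclusion.** The point holds as a detection bias of known direction and unknown size. Followed as written, the plan finds silent ECG abnormalities by schedule in 30 antimony patients and in none of the 60 miltefosine patients, while those of major relevance feed a secondary endpoint. Three events against none would give Fisher p = 0.035, but whether three would occur depends on a rate the protocol does not give. The protocol states no hypothesis test for adverse events, so the p-value only shows how few events matter.

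Two stronger readings are not supported. One is that a difference of a given number of percentage points would arise from scheduling alone: this needs equal true rates in both arms, which section 5.2 gives reason to doubt. The other is that controls will be lost without replacement because of the ECG: no passage says the ECG excludes anyone, and the no-replacement rule in section 3.2.3 concerns withdrawals, which that section defines as after first exposure.

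What is certain on timing is that the Visit 1 row presupposes allocation, and that the protocol does not say how a randomised control patient removed before dosing is counted. The primary endpoint is affected only if such removals occur.

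**What to change.** (a) Flag on the adverse-event form any event found only by a scheduled ECG, and tabulate these events separately. Report between-arm adverse-event incidence both with and without them. Rest the primary safety comparison on events that both arms could show, and state the unequal detection beside it. Dropping the ECG-only events outright is not advised, since that could hide real antimony toxicity.

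(b) Reconcile the flowchart with the order of selection and randomisation by showing the control-arm baseline ECG after randomisation and before the first dose. State that any patient removed on it stays in the comparison as randomised and is not counted as a failure of selection.

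The cost is wording in the flowchart and in sections 3.2.3 and 3.4, one flag and one extra table. The drawback is that the headline comparison must be read beside the ECG table. No change to clinical monitoring is proposed, and no ECGs are added.

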#### 3.3.2 Appointment to the processing and recording

Patients who have been included in evaluations of selection for this research will be documented in an identification list + Patient Record Selection / enrollment.

Each eligible patient will be designated by consecutive numbers, starting at 1 for each age group. The number of patients will be documented in the List of ID + Patient Record Selection / enrollment.

Registration and randomization: the treatment will be allocated according to a randomization list generated by the biostatistics program.

Home Treatment: Treatment should be started up within 2 weeks after completion of evaluations of selection. Otherwise meeting the criteria for eligibility will be restored.

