## **4. STUDY PROCEDURES**

### **4.1 Pre-study evaluation / selection**

Before the first administration of study medication, the investigator will inform the patient verbally and in writing about the potential benefits and any risks associated with their participation in this study and obtain a consent in writing.

The assessment team to verify compliance with the criteria for inclusion / exclusion include:

**Medical history:** General medical history (demographic data, sensitivity to medications and allergies, medical history and surgical significance), concomitant medication, history of leishmaniasis, previous treatments

**Physical examination:** Will be recorded: blood pressure, pulse, weight, height, temperature.

**Medical laboratory tests \*** CBC (no differential), platelets, stool examination  
HIV serology by ELISA or rapid test  
Biochemistry (Na+, K+, urea, creatinine, ALT, AST, LDH, alkaline phosphatase)  
Urinalysis (record of blood and protein only)  
Pregnancy test:  $\beta$ -HCG serum  
Hepatitis C antibodies, HBsAg, anti HBc

\*) All laboratory studies conducted in laboratory validated and reviewed. Abnormal values (values outside the normal laboratory values - 3 benchmarks) will be specifically addressed in patient records.

A second evaluation (at baseline) to verify adherence to the criteria for inclusion / exclusion will be necessary if the time between the assessment team and the first administration of study medication more than two weeks. Include the variables as above for the assessment of selection. In a female patient that requires a waiting period for repayment of a pregnancy test, to repeat the screening tests is unnecessary in the absence of clinical deterioration.

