#### *Variable security:*

Vital parameters

Adverse Events

Laboratory tests (CBC, clinical biochemistry, urine)

Pregnancy test in women who may become pregnant

*Overall assessment:* Reason for discontinuation, overall assessment of tolerability  
A variation of the assessments plus / minus 2 days is acceptable. If these variations are not met, the reason should be documented in the appropriate page of medical records.

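### A woman screened before cycle day 10 may start miltefosine on a single pregnancy test up to 14 days old, with no Day 1 test and no express contraception rule before the first dose

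*Protocol*

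**What the plan says.** Footnote c of the section 4.6 flowchart splits women by the cycle day on which they are screened.

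- **Before day 10 (early branch):** "in the case of a negative pregnancy test before randomization, the treatment can be initiated without waiting period". No second test is asked for.
- **After day 10 (late branch):** "pregnancy test followed by a waiting period of two weeks, during which they should be used adequate contraception". A confirmatory test before randomization follows.

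The time allowed between screening and first dose is set in three places:

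- Footnote a: "Within the 14 days before the 1st dose (except for parasitological examination of lesions, which will be valid within the last 4 weeks". Only lesion parasitology has a different window; the pregnancy test does not.
- Section 3.3.2: "Treatment should be started up within 2 weeks after completion of evaluations of selection".
- Section 4.1 asks for a second evaluation only "if the time between the assessment team and the first administration of study medication more than two weeks".

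The flowchart row "Pregnancy test (women of childbearing age" is marked at Visit 1 and in the Day 14 column; the Day 1 cell is empty. Section 4.2 lists no pregnancy test during treatment. Section 4.3 lists one at the end of treatment: "Pregnancy test in women who may become pregnant".

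On contraception, section 3.2.2 excludes women with "inadequate contraception in females of childbearing potential for treatment period plus 2 months". Section 5.2 says in general terms that pregnancy must not occur during the study or in the 2 months after treatment.

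**The concern.** Footnote c chooses the safeguard by the cycle day at screening, but the risk depends on what happens up to the first dose. A negative test on cycle day 9 says nothing about a conception in the following two weeks, and the protocol allows dosing to begin at the end of them. Late-branch women have both a wait under contraception and a second test before dosing. Early-branch women have neither, even when their first dose falls well into the second half of the cycle.

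Section 5.2 reports that preclinical work pointed to teratogenic potential and that there is no clinical experience in human pregnancy. A site following the schedule to the letter could start the drug in an early pregnancy that a same-day test might have shown.

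**Working it through.** This is date arithmetic; the protocol states no figure of its own to reproduce.

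**Inputs.** Early-branch screening falls on cycle days 1 to 9 (footnote c). The gap from screening to first dose is 0 to 14 days (footnote a, section 3.3.2). The first dose is Day 1. The next pregnancy test is on Day 14 (flowchart) or Day 28 (section 4.3). The visit window of plus or minus 2 days is ignored.

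**Cycle day at first dose** = cycle day at screening + gap.

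| Screened on cycle day | Gap (days) | First dose on cycle day |
|---|---|---|
| 9 | 2 | 11 |
| 1 | 10 | 11 |
| 1 | 14 | 15 |
| 9 | 14 | 23 |

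With the full 14-day gap, every early-branch woman is dosed on cycle day 15 to 23, always past the protocol's own day-10 cut. A woman screened on day 9 passes it after a gap of only 2 days.

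**Contrast between branches.** A woman screened on day 9 may be dosed on day 20 on a test that is 20 − 9 = 11 days old. A woman screened on day 11 must wait until day 25 (11 + 14) and test negative again.

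**Time to the next test, at the 14-day maximum:**

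- Next test on Day 14: 14 + 13 = 27 days between tests, with 13 dosing days (Days 1 to 13) before the second.
- Next test on Day 28: 14 + 27 = 41 days between tests, with 27 dosing days (Days 1 to 27) before the second.

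**Number of women.** The outer ceiling is the 60 patients assigned to miltefosine (section 3.2). If the 2:1 ratio holds within age groups, which is an assumption, 60 × 2/3 = 40 of them are aged 13 to 65. Both figures include males, and the share of women of childbearing potential is not given.

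**Boundary.** The branches are defined as below 10 and above 10, so screening on cycle day 10 belongs to neither.

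**The case against.** The strongest reply is that waiving the wait implies prompt dosing. On that reading the 14 days are an outer validity limit for all screening assessments, and a first dose on day 23 is an unusual delay. That is probably the intent, but the footnote permits a prompt start without requiring one, and the only limits written are 14 days or 2 weeks.

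Contraception is also better covered than the flowchart alone suggests. Inadequate contraception is an exclusion criterion judged at selection, the screening test is a serum β-HCG, and section 5.2 may be meant to include the pre-dose gap. Still, the criterion names treatment and the 2 months that follow, and no sentence gives early-branch women a starting date before the first dose.

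Three further points limit the finding:

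- The 27- and 41-day intervals include time on treatment, which the proposed change does not alter except by adding a Day 1 test for some women. The 41-day figure applies only if a site follows the text and not the Day 14 mark. The exposure at issue is the 0 to 14 days before dosing.
- A repeat test after a gap of a few days adds little and may miss a very recent conception. Contraception from screening would do much of the work.
- The day-10 boundary is a small matter, since a cautious site would choose the late branch.

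**Conclusion.** The concern holds. As written, an early-branch woman may receive her first dose as late as cycle day 23 on one pregnancy test that is 14 days old, with no Day 1 test and no express duty to use contraception in between. This rests on a literal reading of footnotes a and c with sections 3.2.2, 3.3.2 and 4.1. It does not depend on whether the next test falls on Day 14 or Day 28, because both come after first exposure.

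The number of women affected and the pregnancies a repeat test would detect cannot be derived from the protocol. This is a patient-safety point with no bearing on the efficacy comparison. It should be fixed because the possible harm is serious and the remedy is cheap.

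**What to change.** Amend footnote c and the flowchart as follows:

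1. Require adequate contraception from screening for all women of childbearing potential.
2. Limit the no-wait, single-test route to women screened before cycle day 10 whose first dose also falls on or before cycle day 10. Their test can then be at most 10 − 1 = 9 days old.
3. For other early-branch women, require a negative repeat pregnancy test at Visit 2 (Day 1) before the first dose, and mark that cell in the flowchart. This brings the age of the last test from as much as 14 days to 0.
4. Assign screening on cycle day 10 to the late branch (day 10 or later). Women who have completed the two-week wait and the confirmatory test need no further wait.

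The cost is protocol wording, one flowchart mark and a repeat test for some women at a visit already scheduled.
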